**Figure 2 F2:**
[figure not shown]
Recruitment information in the app. **(A)** Advertisement of Volunteer Recruitment for Parkinson's Researches, **(B)** the interface of filling out the ADL form, and **(C)** the interface of completing the ADL form.

### Participant Timeline

As shown in Table 1, the research will be conducted according to the following timeline. First, the subjects will fill out the ADL form and the informed consent form. After evaluation and screening by administrators, persons with PD who fit the inclusion criteria will continue to complete baseline evaluation consisting of eight questionnaires. Then, they will be divided into three groups and participate in a 12-week exercise program. At the end of the program, subjects will complete the evaluation questionnaires. For the next 4 weeks, a follow-up study without exercise intervention will continue. Adverse events will be recorded from week 0 to 16. The questionnaires, same as the ones at baseline, will be filled out again at the end of week 16.

**Table 1 T1:** The time points of data collection.

		**Baseline T0**	**Intervention**	**Intervention end**	**Follow-up**	**Follow-up**
**Assessment**	**Recruitment**	**(Week 0)**	**period**	**T1**	**period**	**end T2**
			**(Week 0–12)**	**(Week 12)**	**(Week 12–16)**	**(Week 16)**
M-EDL		√		√		√
PDQ-39		√		√		√
WOQ-9		√		√		√
FOGQ		√		√		√
CSI		√		√		√
nM-EDL		√		√		√
ADL	√	√		√		√
MFS		√		√		√
Adverse events			√		√	

*“√” means the outcomes will be evaluated in this period. M-EDL, Motor Experiences of Daily Living; PDQ-39, 39-item Parkinson's disease Questionnaire; WOQ-9, The 9-item Wearing-Off Questionnaire; FOGQ, Freezing of Gait Questionnaire; CSI, Caregiver Strain Index; nM-EDL, Non-motor Experiences of Daily Living; ADL, Activities of Daily Living; MFS, Morse Fall Scale*.

### Allocation and Randomization

Randomization is performed with online software (http://www.randomization.com). Participants will receive a number corresponding to Tai Chi group, stretching exercises group, or control group in a randomized controlled table. The allocation result is hidden using a sealed envelope (sequential number). No researcher involved in this study will perform randomization. Researchers responsible for randomization are not involved in the recruitment of subjects, exercise intervention, or outcome evaluation. Similarly, subjects are instructed to withhold the allocation result.

### Intervention

All subjects will take medicine according to prescriptions and record the use of medicine in the Medication Recording module (37). Exercise videos of Tai Chi and stretching exercises will be uploaded to the Exploratory Research module in advance. Each Tai Chi and stretching exercises session consists of 10 min of warm-up, 45 min of exercise, and 5 min of cool-down. The program will last for 12 weeks, with each week containing three sessions of 1-h long exercises, followed by 4 weeks of follow-up without intervention. To ensure safety, subjects will be asked to clear up the surroundings in advance with the assistance of caregivers.

In addition, WeChat and Tencent Meeting will be used for communicating with the participants. Before each intervention, Care-PD will send a notification as well as a text message to remind the participant to exercise according to schedule. During the intervention, a video conference will be initiated that the subjects then join with the camera on. The entire process of the exercise intervention will be supervised and recorded. The researchers will inform subjects on the techniques of exercise, safety precautions, and emergency measures in case of adverse events. At the end of the intervention, the researchers will remind the subjects to log in and inquire about changes in their physical and psychological conditions. The specific plan of intervention is shown in Figure 3. The detailed moves of Tai Chi and stretching exercises are presented in Table 2.

**Figure 3 F3:**
[figure not shown]
The intervention is based on the Care-PD. **(A)** Control group, **(B)** Tai Chi group, and **(C)** stretching exercises group.

**Table 2 T2:** The program of Tai Chi and stretching exercises.

**Type of exercise**	**Descriptions of program**
Tai Chi	1. Preparing and starting form
	2. Up and down form
	3. Bend over form
	4. Curled spine form
	5. Cross wrists form
	6. Go through palms form
	7. Standing on one leg
	8. Flying form
	9. Opening hands and closing hands
	10. Closing form
Stretching exercises	1. Stretching exercises
	2. Neck and upper limb exercises
	3. Moves of waist, abdomen, and lower limbs
	4. Hand moves
	5. Mouth and facial moves
	6. Exercise on the mat

### Tai Chi Group

Tai Chi group joins a 12-week Tai Chi training program that utilizes the Medication Recording module in Care-PD to instruct the use of medicine. Simple Tai Chi, designed by martial art specialists based on the characteristics of PD symptoms, includes 10 exercises: (1) the preparatory and rising, (2) lifting, (3) leaning, (4) spine, (5) wrist-wrapping, (6) palming, (7) freestanding, (8) flying, (9) opening and closing, and (10) retracting positions. The total duration of Tai Chi is 18 min and 55 s. The detailed moves of Tai Chi have been introduced in a previous article (34). The program is remotely supervised by an experienced Tai Chi specialist without the involvement of researchers. The aim of the first 2 weeks of intervention is for the subjects to master every move of the exercise. From week 3 to 12, subjects will perform the full Tai Chi exercise 2–3 times, with 5–10 min of rest in between depending on the fluency of exercises. The number of repetitions is determined by the physical fitness of subjects.

### Stretching Exercises Group

The stretching exercises group joins a 12-week stretching exercises program that also uses the Medication Recording module to instruct the use of medicine. The stretching exercises are designed by a team of experts from Shanghai Tongji Hospital based on the characteristics of PD. It consists of six parts: (1) stretching, (2) neck and upper extremity exercise, (3) waist, abdomen, and lower extremity exercise, (4) hand exercise, (5) mouth and face exercise, and (6) mat exercise. The total duration of the stretching exercises is 14 min and 18 s. Detailed moves of stretching exercises are shown in Supplementary Table 1.

### Control Group

The modules of the Care-PD app available to the control group are consistent with those of Tai Chi group and stretching exercises group except for training programs. The control group will have access to the Medication Recording module but not the exercise videos. After the trial, Tai Chi and stretching exercises videos will be available to all participants in the control group.

### Outcome Assessment

The Exploratory Research module includes eight evaluation questionnaires (Figure 4). The outcomes will be assessed at baseline, the end of exercise intervention, and the follow-up period. Patients or their caregivers will be asked to fill out the questionnaires accurately.

**Figure 4 F4:**
[figure not shown]
Questionnaires of outcome assessment. **(A)** WOQ-9, PDQ-39, and FOGQ, **(B)** CSI, MFS and nM-EDL, and **(C)** M-EDL and ADL.

### Sociodemographic Information

Sociodemographic information including gender, age, height, marital status, living status, education level, and working status will be collected at baseline.

### Clinical and PD-Related Information

Medical history, the number of falls in the past 6 months, lengths of the illness, disease progression, and medication use will also be collected.

### Primary Outcome Measures

#### Motor Aspects of Experiences of Daily Living

The M-EDL is the second part of the Movement Disorder Society–sponsored revision of the Unified Parkinson's Disease Rating Scale (MDS-UPDRS), explicitly designed for measuring cognitive impairment, thought disorder, depression, and motivation (38). It contains 13 items, including speech, saliva and drooling, chewing and swallowing, handwriting, doing hobbies and other activities, eating tasks, tremors, dressing, hygiene, turning in bed, getting out of bed, walking and balance, and freezing. The total score of the M-EDL is 52, and the score of each item ranges from 0 (normal) to 4 (severe) (39, 40). The high score of the M-EDL indicates bad physical fitness. All items have five responses with uniform anchors of 0 = *normal*, 1 = *slight*, 2 = *mild*, 3 = *moderate*, and 4 = *severe*. Total score ranges from 0 to 52, with higher scores reflecting severer conditions.

#### The 39-Item Parkinson's Disease Questionnaire

The PDQ-39 is a 39-item self-report questionnaire, which assesses how often PD patients experience difficulties across eight quality of life dimensions including mobility, activities of daily living, emotional well-being, and stigma, social support, cognition, communication, and bodily discomfort (41). The questionnaire uses a 5-point ordinal scoring system (42) with each dimension total score ranging from 0 to 100, where lower scores represent better QoL (43).

### Secondary Outcome Measures

#### Non-motor Experiences of Daily Living

The nM-EDL is the first part of the MDS-UPDRS (38, 44). The nM-EDL contains eight questions, covering sleep status, tiredness, pain, and other sensations, dysuria (frequent urination, urgent urination or incontinence), constipation, dizziness, and fatigue while standing. The scoring method is the same as the M-EDL. The higher the score, the severer the symptoms.

#### The 9-Item Wearing-Off Questionnaire

The WOQ-9 is capable of diagnosing 95% of wearing-off (WO) after dopaminergic therapy (45). It consists of five questions on motor symptoms and four questions on non-motor symptoms (46). A sum score of the WOQ-9 higher than 2 indicates the occurrence of WO (47).

#### Freezing of Gait Questionnaire

FOG causes falls, limb fractures, and is frequently observed in long-term and terminal PD (48). The FOGQ is used for evaluating the freezing of gait which occurs when patients temporarily feel glued to the ground before stepping forward, accompanied by tremor or drag. Higher FOGQ scores indicate worse conditions of FOG.

#### Caregiver Strain Index

The CSI is a 13-item questionnaire designed to assess the level of strain experienced by caregivers (49), and indirectly reflects the physical fitness of subjects. Answers are either affirmative (1 point) or negative (0 point). The total score of the CSI ranges from 0 (no pressure) to 13 (maximum pressure) (50). A higher score reflects a higher level of caregiver strain. A total score no lower than 7 indicates that the caregiver is under high pressure.

#### ADL

The ADL form is an essential method for evaluating the level of disability and independence of persons with PD (51, 52). The ADL form contains 10 items, including behavior, cognition, and motor skills. The total score ranges from 0 to 100, with higher scores indicating worse ADL.

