## Abstract

**Introduction:** Parkinson's disease (PD) is a common neurodegenerative disease that seriously impairs patients' quality of life, and increases the burden of patients and caregivers. Both drugs and exercise can alleviate its motor and non-motor symptoms, improving the quality of life for PD patients. Telehealth, an increasingly popular tool, makes rehabilitation accessible at home, overcoming the inconvenience of traffic and scheduling. Care-PD is a phone application designed for rehabilitation training, which provides Tai Chi and stretching exercises through tutorial videos as well as an online evaluation system. In this protocol, we will explore the efficacy of Tai Chi and stretching exercises as a PD rehabilitation therapy based on the smartphone application Care-PD.

**Methods and Analysis:** A double-blind, parallel randomized controlled trial will be conducted in this study. The recruitment, intervention, and evaluation processes will be implemented through the Care-PD application. Persons with PD will fill out questionnaires on Activities of Daily Living (ADL), upload the latest case report, and sign the informed consent form in the application. Afterward, doctors and researchers will screen and enroll 180 participants who will be randomly (1:1:1) assigned to Tai Chi group, stretching exercises group, or control group. The subjects will participate in a 1-h exercise session three times per week for 12 weeks, ending with another 4 weeks of follow-up study. Each exercise session includes 10 min of warm-up, 45 min of exercise, and 5 min of cool-down. The primary outcomes are Motor Aspects of Experiences of Daily Living and the 39-item Parkinson's disease Questionnaire. The secondary outcomes include the 9-item Wearing-Off Questionnaire, the Freezing of Gait Questionnaire, the Caregiver Strain Index, Non-motor Experiences of Daily Living, ADL, and Morse Fall Scale. All assessments will be performed at baseline, week 12 and 16.

**Discussion:** Care-PD integrates subject recruitment, intervention, and evaluation, providing a new perspective on clinical rehabilitation for persons with PD. This study will evaluate the efficacy of Tai Chi and stretching exercises on patients' quality of life and disease progression based on a smartphone application. We aim to provide a new rehabilitation training platform for persons with PD.

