### Participants

We will conduct online recruitment (e.g., WeChat) and post advertisements in communities and hospitals to recruit more participants. The researchers in charge of recruitment will remotely guide participants through the registration process. The subjects with PD interested in our research will sign up for the phone app.

Before enrollment, participants will be comprehensively evaluated based on the following items: (1) diagnosis certificate or recent medical records uploaded in Care-PD (Supplementary Figure 1A), (2) Activities of Daily Living (ADL) index scoring (35, 36), and (3) remote video conference evaluation conducted by professional neurologists. The video conference utilizes two cameras (the primary camera and the secondary camera) to remotely monitor the subjects' performance.

We plan to recruit 180 participants who will be divided into three groups using a 1:1:1 randomization formula: Tai Chi group, stretching exercises group, and control group. Every eligible subject will sign the informed consent form in the app (Supplementary Figure 1B).

The inclusion criteria for subjects with PD are:

(1) Diagnosis of idiopathic PD,(2) Age of 40 to 75 years with the ratio of males to females ~1–1,(3) Currently receiving pharmacologic treatment (levodopa) under stable conditions,(4) Scoring over 55 in ADL index,(5) Willingness to cooperate with treatment and sign the informed consent form.

The exclusion criteria are:

(1) Diagnosis of typical PD,(2) Inability to stand for 45 min or complete exercise training,(3) High risk of falls in the next 6 months indicated by Morse Fall Scale (MFS) (37),(4) Severe cognitive or mental disorders verified through remote video conference with the help of caregivers,(5) Inability to use a smartphone or lack of assistance from family members or caregivers to do so.

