### Data Collection, Management, and Analysis

All personal information will be kept strictly confidential, such as age and disease progression. The results will be collected and stored in a database protected by passwords.

Data will be obtained from the Care-PD app and presented as mean ± SE. All statistical analyses will be performed in GraphPad Prism and R studio 3.6.3. Staff with rich experience will independently complete the processing and cleaning process of data. Baseline data between groups will use one-way ANOVA for continuous variables and normal distribution, Wilcoxon test for continuous variables and non-normal distribution, and chi-square test for categorical variables. Repeated-measure ANOVA is used to evaluate the efficacy of Tai Chi and stretching exercises on QoL and PD progression over 12 weeks (within-group). A mixed-model repeated-measure ANOVA is used to compare the difference between Tai Chi, stretching exercises, and the control (between-group).

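### The ADL outcome definition and the ADL inclusion criterion imply opposite scoring directions, so one of the two must be wrong

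*Protocol article*

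**What the plan says.** In the Secondary Outcome Measures, the ADL section describes a 10-item form: "The ADL form is an essential method for evaluating the level of disability and independence of persons with PD". It then fixes range and direction: "The total score ranges from 0 to 100, with higher scores indicating worse ADL".

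The Participants section uses an ADL index as inclusion criterion (4): "Scoring over 55 in ADL index". No upper bound is given. The exclusion list in the same section includes "Inability to stand for 45 min or complete exercise training", and separately a high six-month fall risk on the Morse Fall Scale.

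The ADL form is used both for screening and as an outcome. The Participant Timeline section opens with screening: "First, the subjects will fill out the ADL form and the informed consent form". Table 1 then marks ADL at recruitment and at weeks 0, 12 and 16, and the Abstract lists it among the secondary outcomes. The article describes no second version of the form, no reversed scoring and no separate direction for screening.

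**The concern.** A threshold on a scale has a meaning only once the direction of the scale is known. Here the one explicit statement of direction makes the threshold select poor daily function, while the neighbouring exclusions select for good physical function. If staff apply the text as published, one of two things goes wrong: the trial population is drawn from the wrong side of the cut-point, or the ADL result is described the wrong way round.

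The article also says, under Adherence Promotion, that immediate assessment results are meant to reinforce adherence, and in the Discussion that patients can follow their progression in the app. If the app carries a wrong direction for ADL, participants could be shown improvement as worsening, or the reverse, while the trial is running. The article does not show how the app presents the ADL score, so this is a possibility to check.

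**Working it through.** The article gives no figure to reproduce on this point. The check is to apply the threshold to the scale under each possible direction and compare the result with the exclusions.

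**Inputs.** Range 0 to 100, higher is worse (ADL section). Threshold: score over 55, no upper limit (Participants, inclusion 4). Exclusions for inability to stand 45 minutes or complete training, and for high fall risk (Participants). Between-group analysis: mixed-model repeated-measures ANOVA (Data Collection, Management, and Analysis).

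**Case A: higher is worse, as the ADL section states.**
- Not admitted: 0 to 55, which includes the best possible score of 0.
- Admitted: above 55 up to 100, which includes the worst possible score.
- Re-expressed as independence, I = 100 − S, the rule S > 55 becomes I < 100 − 55 = 45. The criterion then admits only people below 45 on a 0 to 100 independence scale.
- The exclusions work in the other direction: they remove people with poor standing tolerance, inability to train or high fall risk. The combination is not formally impossible, since someone could be dependent in daily activities and still stand for 45 minutes. But the inclusion rule would turn away the people best able to meet the exclusions, and the article gives no reason for wanting that.
- In this case the outcome definition is correct and a fall in ADL score is properly read as improvement.

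**Case B: higher is better.**
- "Scoring over 55 in ADL index" becomes a minimum level of independence and agrees with both exclusions.
- The ADL section is then reversed. A rise from week 0 to week 12 or 16 is an improvement, but the published definition would have it reported as a deterioration.

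**Effect on the analysis in Case B.** Let the true direction be that of Y, and suppose results are read as if it were that of 100 − Y. Any mean difference d on Y becomes (100 − Y₁) − (100 − Y₂) = −d. Sums of squares depend on d², so the F statistics and p-values of the ANOVA are identical on either orientation. The analysis would therefore give no sign of the error. The stored scores are also unchanged; only the statement of benefit or harm reverses.

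**Can both consequences hold?** No. Case A has a faulty eligibility rule and a correct outcome direction. Case B has a coherent eligibility rule and a reversed outcome direction.

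**The case against.** The strongest reply is that this is a one-word slip in a journal article. Because the threshold makes sense if higher means more independent, the word giving the direction in the ADL section is the likelier error. The form loaded in the app determines the scores, and actual screening may be entirely sound. That is plausible, and the exclusions support it. But the article does not say so, and a reader cannot tell which statement the app and the staff follow.

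A second reply concerns safety. A reader might infer that the literal rule puts disabled people into unsupervised exercise at home. The documents do not support this. The Intervention section says sessions are held by video conference, supervised and recorded, and the Tai Chi Group and Adherence Promotion sections confirm remote supervision. Screening also includes medical records and a two-camera evaluation by neurologists, and the standing, training and fall-risk exclusions apply whatever the ADL score. These safeguards limit the harm. They do not bring back the more independent patients whom the literal rule would reject.

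A third reply is that the statistical damage is small. This is largely right: ADL is one of six secondary outcomes, test results do not depend on orientation, and a wrong description can be corrected at reporting.

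**Conclusion.** The contradiction stands. The ADL section and inclusion criterion (4) cannot sensibly be applied together beside the article's own exclusions, and nothing else in the article reconciles them. Followed as written, the plan yields either an eligibility rule that admits the more dependent patients and rejects the more independent ones, or a reversed reading of a secondary outcome at weeks 12 and 16.

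The size is bounded. The two consequences are alternatives, and it would be wrong to infer that the trial both selects the wrong patients and misreports the outcome. It would also be wrong to infer that screening of all 180 participants is affected: 180 is the number to be enrolled, and eligibility is affected only in Case A. The primary outcomes (M-EDL and PDQ-39) and the sample size calculation do not use the ADL score.

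The conclusion assumes that the ADL index in the inclusion list and the ADL form in the outcome section are the same instrument with the same scoring. The timeline and Table 1 indicate this. The scoring key itself is not shown, so the documents do not settle which statement is wrong.

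**What to change.** Before screening:

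1. Check the scoring key of the ADL form as loaded in Care-PD and record its direction.
2. Reconcile the Participants and ADL sections so that the inclusion criterion and the outcome definition use the same direction. If the key has higher as better, the outcome definition needs correcting. If it has higher as worse, the clinical team must reconcile inclusion criterion (4) with the standing, training and fall-risk exclusions.
3. State the direction of benefit for ADL once, and use that statement for the analysis, the reporting and any feedback shown in the app.

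The cost is a one-line protocol correction and one check of the app's scoring rule. The sample size, visit schedule and statistical model do not change.
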